#### Participant recruitment and screening

Consecutive women attending primary health care-based antenatal care in two primary care facilities will be the target sample for recruitment into the study (Fig. 1) after the research staff obtains informed consent. The research staff will check initial eligibility of antenatal attendees based on information available from the clinical records (gestational age, age, co-morbid conditions and residence). Eligible women will be invited to provide informed consent to an initial screen for depressive symptoms associated with functional impairment using the PHQ-9 and the PHQ-9 disability item. The disability item asks ‘Over the last two weeks, how difficult have these problems made it for you to do your work, take care of things at home, or get along with other people?’ The response options are: ‘Not difficult at all’ = 0, ‘somewhat difficult’ = 1, ‘very difficult’ = 2 or ‘extremely difficult’ = 3. The MINI will be administered to women who endorse any frequency of suicidality on the ninth item of PHQ-9. Women with risk of suicide (MINI≥17) [48] will be excluded from the study and referred for review by a mental health-trained primary care worker [31] who will employ mhGAP [49] to assess risk of suicide. The research staff will facilitate women’s attendance of services at the referral sites and their transportation costs to access care.

Any woman who is found to be eligible following the initial screen will receive written and verbal information about the study from research staff and invited to participate. Women who provide informed consent to participate in the trial will receive a fully structured baseline interview after receipt of their routine clinical care.

Participants’ costs incurred to attend research interviews and PST sessions will be reimbursed. Time spent during research interviews will be compensated, but time spent attending PST sessions will not be compensated to avoid incentivising engagement with the intervention. The healthcare workers will be compensated for their additional effort in the trial.

#### Sample size

Fifty participants (25 in the intervention and 25 in the enhanced usual care group) will be recruited for this feasibility trial. This sample size will enable us to detect a dropout rate of 7% with 95% confidence interval and a 5% margin of error [50]. A sample size of 24–50 is recommended for feasibility studies [51].

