**Methods:**

Design: A randomised, controlled, feasibility trial and mixed method process evaluation. Participants: Consecutive women attending antenatal clinics in two primary care facilities in rural Ethiopian districts. Eligibility criteria: (1) disabling levels of depressive symptoms (Patient Health Questionnaire (PHQ-9) score of five or more and positive for the 10^th^ disability item); (2) gestational age 12–34 weeks; (3) aged 16 years and above; (4) planning to live in the study area for at least 6 months; (5) no severe medical or psychiatric conditions. Intervention: Four sessions of adapted PST delivered by trained and supervised antenatal care staff over a maximum period of eight weeks. Control: enhanced usual care (EUC). Sample size: *n* = 50. Randomisation: individual randomisation stratified by intimate partner violence (IPV). Allocation: central phone allocation. Outcome assessors and statistician masked to allocation status. Primary feasibility trial outcome: dropout rate. Primary future efficacy trial outcome: change in PHQ-9 score, assessed 9 weeks after recruitment. Secondary outcomes: anxiety symptoms, trauma symptoms, intimate partner violence, disability, healthcare costs at 9 weeks; postnatal outcomes (perinatal and neonatal complications, onset of breast feeding, child health) assessed 4–6 weeks postnatal. Other trial feasibility indicators: recruitment, number and duration of sessions attended. Audio-recording of randomly selected sessions and in-depth interviews with purposively selected participants, healthcare providers and supervisors will be analysed thematically to explore the acceptability and feasibility of the trial procedures and fidelity of the delivery of PST.

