#### Process evaluation outcomes

The nested process evaluation investigates two categories of feasibility/implementation outcomes: trial procedure feasibility and acceptability (see Table 2) and implementation of delivery of PST (Table 3). The primary outcome for feasibility trial procedures is dropout rate. Dropout will be defined as the number of women lost to follow up at either of the follow up assessments. Secondary outcomes related to trial procedures and data collection procedures are listed in Table 2. These include participant recruitment rate, feasibility and suitability of eligibility criteria, feasibility of data collection procedures (clarity of baseline questionnaires, characteristics of outcome measures such as missing data, time needed to complete the questionnaires and data collection), adequacy of masking and practical administrative challenges and acceptability of trial procedures (number of refusals to recruitment and screening; qualitative exploration of experience of trial procedures).

**Table 2 Tab2:** Outcomes of trial procedures

Feasibility outcomes	Data source	Feasibility success	Timing
Feasibility of recruitment			
• Dropouts from the trial/completion of sessions	screening logs, supervision minutes and session records	50% or more women complete sessions	Pre- and during intervention
▪ Feasibility and suitability of eligibility criteria restrictive/too inclusive	Administrative (screening logs) Proceedings of weekly supervision meeting (Agenda: suitability of eligibility)	# of women excluded due to each exclusion criteria	Pre-intervention
Feasibility of data collection procedures			
▪ Clarity of baseline questionnaires (layout, instructions, order of tools))	Proceedings of weekly supervision meeting (Agenda: clarity, time and acceptability of items	20 minutes to complete baseline and follow up battery	Pre-intervention
▪ Characteristics of outcome measures (SD of the outcome and missing data)	Outcome assessment tools	Less than 5% missing data	Post baseline assessment
▪ Time needed to complete questionnaires (reasonable or burden to participants)	Time recorded on questionnaire FGD with supervisors and research assistants	20 minutes to complete baseline and follow up battery	Pre-intervention
• adequacy of masking of assessors and time needed to collect and analyse the data	Administrative documents FGD with supervisors and research assistants		since start of recruitment

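### Fifty women do not give a 5-point margin of error around a 7% dropout rate; the 95% margin is about 7 points overall and about 10 points per arm

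*Protocol article*

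**What the plan says.** The Sample size section fixes the number: "Fifty participants (25 in the intervention and 25 in the enhanced usual care group) will be recruited for this feasibility trial". It then gives the precision that this number is meant to deliver: "This sample size will enable us to detect a dropout rate of 7% with 95% confidence interval and a 5% margin of error", with one cited reference. The next sentence adds a general recommendation of 24–50 participants for feasibility studies, from a second reference.

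The quantity concerned is the main outcome of the study. The abstract lists it as "Primary feasibility trial outcome: dropout rate", and the section on process evaluation outcomes repeats this: "The primary outcome for feasibility trial procedures is dropout rate". The same section defines it: "Dropout will be defined as the number of women lost to follow up at either of the follow up assessments". It is therefore to be estimated as one proportion of the randomised women. The article states no finite population, no one-sided limit and no confidence level other than 95%.

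**The concern.** Sample size, expected proportion, confidence level and margin are all given in one place, so any one of them can be checked against the other three. They do not agree. With a proportion near 7% and only 50 women, three or four dropouts are expected (0.07 × 50 = 3.5), and so few events cannot fix the rate to within 5 points.

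The trial exists to inform a fully powered efficacy trial, and a natural use of its primary outcome is to set that trial's allowance for attrition. A reader who trusts the sentence would take an observed rate near 7% as ruling out dropout above 12%. The data would in fact be compatible with about 17% to 18%.

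**Working it through.** **Inputs**, all from the Sample size section: n = 50 in total and 25 per arm; p = 0.07; confidence 95%; margin d = 0.05, read as an absolute half-width of 5 percentage points. The section does not say whether the interval is one- or two-sided. Two-sided (z = 1.96) is taken as the ordinary meaning, and one-sided is tried below.

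**1. Attempt to reproduce the plan's figure.** The standard formula for estimating one proportion is n = z² p(1 − p) / d².

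- n = 1.96² × 0.07 × 0.93 / 0.05² = 3.8416 × 0.0651 / 0.0025 = 100.04, so about 100 women.
- The plan has 50. The figure is not reproduced.

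**2. Margin that the planned numbers give**, from z √(p(1 − p)/n):

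- n = 50: 1.96 × √(0.0651/50) = 1.96 × 0.03608 = 0.0707, or 7.1 points. This is 41% wider than stated (7.07/5 = 1.41).
- n = 25: 1.96 × √(0.0651/25) = 1.96 × 0.05103 = 0.100, or 10.0 points.

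With 50 women, a 5-point margin holds only if dropout is about 3.4%.

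**3. Intervals better suited to few events.** The normal approximation is rough here. At n = 50 its lower limit is 7.00 − 7.07 = −0.07 points, just below zero. The alternatives are wider:

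| Method | Data | 95% interval | Half-width |
|---|---|---|---|
| Wilson | 7%, n = 50 | 2.6% to 17.5% | 7.5 points |
| Wilson | 7%, n = 25 | 1.8% to 23.7% | 10.9 points |
| Clopper–Pearson | 3/50 | 1.3% to 16.5% | 7.6 points |
| Clopper–Pearson | 4/50 | 2.2% to 19.2% | 8.5 points |
| Clopper–Pearson | 2/25 | 1.0% to 26.0% | 12.5 points |

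**4. Other readings of the sentence.**

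- *One-sided 95%* (z = 1.645): the margin at n = 50 is 1.645 × 0.03608 = 0.0594, or 5.9 points. A 5-point margin needs n = 1.645² × 0.0651 / 0.0025 = 70.5, so 71 women.
- *Chance of seeing at least one dropout*, n = ln(0.05)/ln(1 − p): at 7%, 41.3, so 42 women; at 5%, 58.4, so 59 women. Fifty women give 1 − 0.93⁵⁰ = 97.3% at a 7% rate. The formula contains no margin of error and does not return 50.
- *Finite population correction*, n = n₀ / (1 + (n₀ − 1)/N) with n₀ = 100: a population of N = 100 gives 50.3, N = 200 gives 66.9 and N = 500 gives 83.5. Only a closed population of about 100 women returns 50, and the article states none.

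**5. Probability attached to ±5 points at n = 50.** By the normal approximation it is 83%. The exact binomial probability that the observed rate falls within 5 points of a true 7% is 91.5% (1 to 6 dropouts, endpoints included). That value depends on both endpoints falling exactly on possible counts. At true rates of 6.9% and 7.1% it is 84% and 82%. It is below 95% in each case.

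**The case against.** The arithmetic under the standard formula is hard to dispute. The case on the other side concerns what follows from it.

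- **Nothing in the plan operates on the 5-point margin.** The outcomes are described, not tested. No stopping or progression rule uses 5% or 12%, and the success criterion beside dropout in Table 2 is that half or more of the women complete sessions. This stands: it limits the consequence to what readers are told about precision.
- **The sample size has a second basis.** The 24–50 recommendation supports 50 independently. This also stands, so the finding is against the precision statement and not against recruiting 50 women. The recommendation says nothing about a 5% margin, however, and the precision statement is the only calculation offered.
- **The per-arm figure contradicts nothing.** The article attaches its margin to the total of 50 and claims no precision per arm. This is correct: the 10-point figure extends the point to a breakdown that a two-arm trial will probably report.
- **The wording may be loose.** "detect a dropout rate of 7"% could mean seeing at least one dropout, for which 50 women suffice, with the 5% a clumsy restatement of 1 minus 95%. This cannot be excluded as the intention, but it leaves "a 5% margin of error" wrong as printed.
- **A cited source or a finite population might explain it.** The reference was not available to this review. The sentence could be saved only by a population of about 100, which fits poorly with consecutive recruitment of antenatal attendees to inform a later trial.
- **Later planners can compute their own interval from the observed count.** True, and an exact 7% of 50 cannot occur, since it is 3.5 women. The published claim would still misdescribe what the study can show about its primary outcome.

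**Conclusion.** The precision stated for the primary outcome is wrong as written. From the section's own inputs, 50 women give a two-sided 95% half-width of 7.1 points at 7% dropout, against the 5 points claimed; 5 points would take about 100 women. Small-sample methods make the shortfall larger, with upper limits of about 17% to 19% for three or four dropouts among 50. For 25 women the half-width is 10.0 points.

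This rests on reading the margin as an absolute half-width, the interval as two-sided and the population as effectively unlimited. Making it one-sided does not close the gap, and the finite population that would do so is not in the document. The choice of 50 as a feasibility sample is not called into question.

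**What to change.** Keep 50 women and replace the precision sentence with one the numbers support, for example: with 50 women and an expected dropout of 7%, the 95% Wilson interval will run from about 3% to 18%, and with 25 women per arm from about 2% to 24%. Say that dropout will be estimated, not detected, and report it overall and by arm with Wilson or exact intervals, since a symmetric margin fits poorly at this event rate.

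If 50 was in fact chosen from the 24–50 recommendation, say so and remove the 5% margin. If a 5-point margin is truly required, the plan needs about 100 women.

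The first two options each cost one edited sentence and a less favourable stated precision, with no added participants and no change to the design. The third doubles recruitment.

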#### PST intervention

PST is a commonly used psychotherapy [38, 52] that has comparable efficacy to other psychotherapies such as behavioural activation, cognitive behavioural therapy and social skills training and medication [53, 54]. The PST approach assumes that depressive symptoms are the negative consequences of maladaptive coping in response to problems [55]. The intervention applies principles of evidence-based problem-solving therapy [55] to improve a person’s problem solving and coping skills. In this approach, there are three phases. In the first phase, women are helped to identify the most important things in their life. In the second phase, they identify a list of problems that challenge attainment of important goals in their life and classify the problems into three categories: ‘Problems that are upsetting but not relevant to the most important things in one’s life’ (group A); ‘Problems that are important but, insoluble’ (group B); and ‘important and soluble problems’ (group C). Any psychological therapy should be adapted to the cultural setting to ensure effectiveness, acceptability and feasibility [56]. PST has been contextually adapted and manualised for pregnant women with antenatal depressive symptoms in rural Ethiopia ([name] 2020, unpublished). The adaptation was based on the Medical Research Council guidelines for developing and evaluating complex interventions [34] and the ADAP-ITT approach [35]. This comprised a series of theory of change workshops, adaptation workshops and in-depth interviews with women with a history of perinatal depression and healthcare providers, and discussions after role play (theatre test).

Participants randomised to the intervention arm will receive four individual sessions of locally adapted and manualised PST, along with enhanced usual care, at a time convenient to them in a private room of the PHC facility. Intervals between sessions will range from a minimum of 2 days to a maximum of 2 weeks over a period of 8 weeks ensuring that all sessions are completed during pregnancy. The first session will last for 1 h and the remaining sessions will last for approximately 40 min each.

The general approach to treatment is introduced in the first session, during which the structure of PST is fully explained, the participant identifies the most important priorities in her life and a list of her current problems is established and classified into the three problem categories: group A, group B and group C problems. In each session, at least one ‘problem busting session’ or ‘group C’ problem, important to the participant and that can potentially be solved, will be discussed and the participant will agree a ‘take home activity’ based on that problem.

The second session will recap on the previous session, review the outcome of the first take-home activity, introduce problem solving strategies for problems categorised as ‘group A’ and include one problem busting session for a group C problem. The third session will review the outcome of the second take-home activity, introduce strategies for problems categorised as ‘group B’ and include one or two problem busting sessions for ‘group C’ problems. The final session will recap the third session and include a problem busting session for any problems which the participant wishes to prioritise.

Trained healthcare workers will deliver the intervention under the supervision of an Ethiopian clinical or counselling psychologist (master’s level) or psychiatrist/psychiatric resident trained in psychological therapies. Healthcare worker training will consist of (a) a 5-day classroom-based training course which includes training on counselling and communication skills as well as PST-specific skills, and (2) accelerated delivery of four sessions of PST, using high-intensity supervision and feedback to build competency [57, 58]. Competency will be established using the Enhancing Assessment of Common Therapeutic factors (ENACT) scale [57, 58] administered by trained clinicians. The healthcare worker will be required to score level 3 (‘Done Well’) out of the three levels: (‘Done Well’, ‘Done partially’ and ‘Need improvement’) on each of the competencies in order to participate in the trial. Feedback will be obtained from women receiving the accelerated PST intervention in the form of three structured questions with open-ended responses: (1) What parts of PST did you find helpful? (2) What parts of PST were unhelpful/need to be improved? How should they be improved? and (3) How convenient was it for you to attend PST? How could this be improved? All intervention sessions will be audio-recorded. A random selection of sessions will be assessed by an expert who has been shown to rate reliably with kappa greater than or equal to 0.80 for repeated scoring. A checklist that contains five dimensions of fidelity [59] will be adapted and used to assess the audio records and then to give feedback focussed on intervention fidelity and core competencies in PST and communication skills. The five dimension of fidelity include (1) adherence (extent to which program components such as program content, methods and activities are delivered as prescribed by the model); (2) exposure (number of sessions or contacts, attendance and the frequency and duration of sessions); (3) quality of delivery (provider enthusiasm, interaction style, respectfulness, confidence and ability to respond to questions and communicate clearly); (4) participant responsiveness (participants’ level of interest in the program; perceptions about the relevance and usefulness of a program; and their level of engagement, enthusiasm and willingness to engage in discussion or activities); and (5) program differentiation (degree to which the critical components of a program are distinguishable from each other and from other programs).

Clinical records and consent forms will be kept in the research office for confidentiality. Research staff will use telephone contact to follow up participants who withdraw without reporting to the research office in order to check for unreported adverse events.

#### Enhanced usual care

Participants allocated to the enhanced usual care arm will receive usual antenatal care which focuses on advice about reproductive and family health issues and information about sources of general support. In addition, the Federal Ministry of Health in Ethiopia has prepared evidence-aligned guidelines on how to care for mental health problems in primary health care and maternal care settings [60]. According to the guideline, primary healthcare staff are expected to detect mental health problems and to provide basic mental healthcare (non-specific psychosocial care for all and supervised prescription of antidepressant medication depending on severity) [61]. All healthcare providers participating in the trial will have been trained in the World Health Organisation’s mhGAP for a minimum of 5 days, as per the mental health scale-up plans of the Federal Ministry of Health. As mhGAP has not been implemented at scale in Ethiopia, this represents an enhancement in usual care [62, 63].

Participants allocated to enhanced usual care and their healthcare providers will be informed about the results of screening and will receive an information sheet and sources of general psychosocial support. These women will attend three contacts: one pre-intervention assessment and two follow-up assessments at 9 weeks after recruitment and 4–6 weeks after childbirth.

#### Assessment of trial participant outcomes

A list of assessment variables and details about their measurement is described in Table 1. Assessment will be conducted at three time points: pre-intervention (T0; baseline), 9 weeks after recruitment (T1; first follow-up) and 4–6 weeks after delivery (T2; second follow-up).

**Table 1 Tab1:**
[figure not shown]
Schedule of enrolment, interventions and assessments

The primary outcome for a future efficacy trial will be change in PHQ-9 score using the locally validated Amharic version of PHQ-9 [64], assessed at T0, T1 and T2. The PHQ-9 has been widely used as a clinical outcome measure of treatment for depression [65, 66]. In Ethiopia, PHQ-9 has been validated in antenatal women [67] and in primary care settings in the neighbouring district of the current study, with the optimal cut-off point indicating probable depression identified as five or more in primary care attendees [47]. At that cut-off, PHQ-9 had a sensitivity of 83.3% and specificity of 74.7% for detection of major depressive disorder. In previous studies, a 50% reduction in PHQ-9 depressive symptom scores [66] after 6–8 weeks was defined as treatment response. A 50% reduction of PHQ-9 score at nine weeks (T1) follow up will be defined as a treatment response for future efficacy trial.

Secondary outcomes to be collected at T0, T1 and T2 are disability (change in WHO disability Assessment Scale, WHODAS, score) [68], anxiety [Generalised Anxiety Disorder-7 scale; GAD-7) [69], PTSD symptoms checklist (PCL-5) [70, 71], intimate partner violence (non-graphic IPV test with five items [72] and WHO multi-country study questions [73]), number of emergency healthcare visits and costs (locally adapted Client Service Receipt Inventory (CSRI) [74]).

At T2, only (4 to 6 weeks postnatal) self-reported information on delivery setting, prolonged labour, sepsis, unsafe abortion, perinatal mortality (stillbirth and neonatal mortality), time of onset of breast-feeding and child health (maternal report of diarrhoea, fever and refusal to breast feed) will be collected.

Potential mediators will be assessed at T0, T1 and T2: attitudes towards gender roles (attitude towards gender roles scale [75]), mastery (Multicultural mastery scale [76]]), self-efficacy of coping with depression (adapted self-efficacy scale [76]) and perceived social support (Oslo Social Support Scale (OSS-3)), previously used in Ethiopia [77] (Table 1).

At T0, a questionnaire will collect data about socio-economic and demographic characteristics of the participants (age, education, marital status, age at marriage, husband’s occupation and educational level, residence and pregnancy intention), obstetric history, including parity, pregnancy intention and gestational age, past psychiatric history and list of traumatic experiences. An item from Ethiopian Demographic Health Survey (EDHS (previously used in our study [7]) will be used to assess pregnancy intention.

